## 3. Discussion

Living and experiencing UI affects the quality of life among nonpregnant and pregnant women [3,57]. Even though no studies have explored the economic burden of UI during pregnancy [58], UI among women has been stated as a high economic burden as it affects a person psychologically, socially, and financially [59]. Pregnant women face barriers seeking help by assuming that UI “normally” occurs during pregnancy and UI will resolve after giving birth. Hence, an effective intervention is essential to deliver the correct conservative management for UI during pregnancy, either pelvic floor muscle training (PFMT) or Kegel exercise.

KEPT-app trial is a single-blind, pragmatic, cluster RCT that will be implemented with this pilot test’s findings. Being a pragmatic study, which is recommended as it is near to the real current situation, challenges of uncertainty must be well informed. This pilot trial aims to identify the potential challenges of recruitment from one single centre before involving multiple centres for the actual trial. There are various restrictions in collecting data from multiple centres due to the COVID-19 pandemic. Information from a single centre feasibility trial will provide valuable information on whether it is suitable to proceed with data collection from multiple study sites. Therefore, alternatives need to be planned and prepared. Any amendments to the full study protocol will be informed via an erratum to the previously published phase III study protocol [26].

This pilot study will evaluate innovative features of the app such as an embedded electronic consent form. Obtaining informed consent from participants is an essential research ethics process in conducting studies. This consent form will be different from the usual online surveys where it requires the users to sign on the app. The act of physically signing the form is a form of persuasive technique [60], which may contribute towards their commitment towards the study. This electronic consent form may be an alternative process for obtaining participants’ informed consent in future studies where face-to-face methods are not possible.

Additional strengths of this study include evaluating the feasibility and challenges of implementing mobile apps in the maternal and child health setting in a primary care clinic. These questions are vital to be answered with evidence from the results of this pilot study.

The limitation of this study will be that it only evaluates the feasibility of the study from a single centre. There may be other additional implementation findings when the full study is conducted over multiple centres. However, this issue cannot be avoided due to the various restrictions related to conducting research in health facilities during the COVID-19 pandemic. 

## 4. Conclusions

As a conclusion, this study will hopefully understand the feasibility and acceptability of this mHealth app and the intervention study design for future full-scale clinical trials.

## Figures and Tables

**Figure 1 ijerph-18-04792-f001:**
[figure not shown]
Pilot study flowchart.

**Figure 2 ijerph-18-04792-f002:**
[figure not shown]
Conceptual framework of KEPT-app.

**Table 1 ijerph-18-04792-t001:** Study outcomes of the KEPT-app trial.

Primary Outcome	Information
Acceptability and feasibility (usability) of the app.	The acceptability will be assessed for its content, comfort, complexity, and other factors. (1) How many stars would you use to recommend this app to your friends? (2) How many stars would you rate the content of this app? (3) How many stars would you rate the comfort using this app? (4) How many stars would you rate simplicity using this app? (5) How many stars would you rate the recruitment process using this app? (6) How many stars would you rate the quality of the app? (7) Factors influenced/hindered using this app? (8) What motivates you to continue the PFMT? (Further information will be collected via qualitative data feedback) Malay-mHealth App Usability Questionnaire (M-MAUQ) will be used [46,50] to assess the ease of use, interface, satisfaction, and the usefulness of mHealth apps to the end user.
**Secondary Outcomes**	**Information**
The log system records.	The recruitment rates, dropout rates from the registry, and the log system records.
International Consultation on Incontinence Questionnaire—Urinary Incontinence Short Form (ICIQ-UI SF) [29,30].	To measure the urinary incontinence score at baseline, one-month, and two-months post-interventions.
Exercise Adherence Rating Scale (EARS) [51]	Increasing PFMT adherence from lowest score (0) to maximum score (24) of Exercise Adherence Rating Scale (EARS). To measure the adherence score at baseline, one-month, and two-months post-interventions.
Self-Efficacy Scale For Practicing Pelvic Floor Exercise Questionnaire (SESPPFE) [52]	Improving self-efficacy by scores of higher than 70% of the self-efficacy scale for practicing pelvic floor exercise questionnaire (SESPPFE). To measure the self-efficacy score at baseline, one-month, and two-months post-interventions.
Patient Education Materials Assessment Tool (PEMAT) [47].	To assess the understandability and actionability of the video. To validate the video at one-month post intervention.
Knowledge, Attitude, and Practice towards Pelvic Floor Muscle Training [53]	To assess the knowledge, attitude, and practices towards PFMT at baseline, one-month, and two-months post-interventions.
International Consultation on Incontinence Questionnaire Urinary Incontinence—Lower Urinary Tract Symptom quality of life (ICIQ-LUTSqol) [29,30].	To assess the quality of life among pregnant women with UI at baseline, one-month, and two-months post-interventions.

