## 2. Materials and Methods

Design overview: This pilot study will use a single-blind, single-centre, parallel, randomised controlled trial (RCT) design that will incorporate individualized treatment flexibility, as in a real-world setting, and provide the future study’s feasibility process [26]. The study protocol was designed and reported according to CONSORT (Consolidated Standards of Reporting Trials) extension for randomised pilot and feasibility trials [27,28].

Participants (eligibility criteria): The eligible participants are: (1) pregnant women aged over 18 years old, (2) any parity at 26–27 weeks’ gestation, (3) with either stress UI or mixed UI according to the International Consultation on Incontinence Questionnaire—UI Short Form [29,30], and (4) Malaysian citizens. Other citizens will be excluded as the primary language used in this study will be Malay, the national language of Malaysia.

Additionally, pregnant women with chronic medical problem(s) before pregnancy, complicated pregnancies, or conditions with which it is not advisable to practise PFMT will be excluded.

Recruitment and withdrawal: This study will be conducted at one primary care clinic in the Hulu Langat district under the same management as the future study [26]. The recruitment process will follow the future study, whereby pregnant women will be invited from a poster announcement [26]. They will then contact the research assistant (RA) via WhatsApp or Short Message System (SMS) for the eligibility screening process. Once a pregnant woman is eligible to join the study, the RA will provide her with a link to download the app for the consent forms. (Figure 1)

All study participants can withdraw at any time during the trial with or without any reasons. The RA will contact those who have withdrawn to obtain reasons and their experiences joining this pilot study. This finding will be analysed and given as input into the barriers that will add to future study modifications.

For the sample size, an analysis suggested that 12 participants per group is an appropriate sample in a feasibility study [31] and another review stated that 15 participants per group could be adequate for moderate effect sizes [32]. A pilot randomised controlled trial for an expected small effect size should have 25 participants per arm [33]. However, considering a possible 20% dropout rate, the final sample size will be 64 participants with 32 participants per arm.

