The KEPT-app feasibility will be defined as KEPT-app’s extent of successfully being used or carried out in a primary care clinic setting [45]. The app feasibility will be assessed along with the usability assessment, which can assess the ease of use, interface, satisfaction, and mHealth app usefulness [46]. Additionally, the PFMT education video embedded in the app should assess its understandability and actionability [47]. 

Secondary outcomes are as follows; (1) feasibility of recruiting the study participants, which include numbers and proportions of participants recruited, screened, consented, and numbers with their reasons for withdrawals; (2) face validation on the educational video embedded in the app; (3) appropriate training time in achieving the advanced skill level; (4) control group’s barriers continuing the study; (5) barriers and suggestions for using the app; (6) the knowledge, attitude, and practice of PFMT; and (7) quality of life.

Training time will be recorded automatically via the app and a reminder will be delivered (during the evening) if no PFMT is recorded on that day. There will be three training skills: beginner (2 s each contraction), intermediate (6 s each contraction), and (10 s each contraction). The pregnant women are scheduled for ten repetitions each set and must complete three sets every day. The time recorded will be analysed using the algorithm to measure which training skills will change their self-efficacy and adherence.

It is essential to determine the KEPT-app’s preliminary effectiveness to improve the PFMT skills of pregnant women. The time recorded by the pregnant women will be analysed with the self-efficacy improvements and adherence towards PFMT. Additionally, the recorded time will be analysed with the UI changes within the group.

Additional qualitative data collection will be used to further understand any barriers or suggestions from the study participants. The expenditures during the study, for example, the cost of absorbent pads, participant’s salary, and cost of laundry where applicable, will be compared between the groups to assess the cost-effectiveness.

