### 2.2. Statistical Analysis

The primary analysis of this pilot study will be by descriptive analysis to concentrate on the feasibility outcomes. The recruitment number and the proportion of participants screened, consented, and randomised will be presented. Additionally, the information of the dropouts will be presented with their reasons in the results.

The results of study outcomes and validation of educational video will be analysed. Exploratory analysis of the effect sizes for PFMT adherence will be conducted by mixed-effects regression analyses, controlling for significant baseline characteristics, such as age, parity, educational status, and income status. For the cost-effectiveness analysis, expenditures during the study will be compared between the groups using the multiway sensitivity analysis.

As the data will be sent via the app, the system will collect the data and store it in a secured and encrypted cloud storage. The researcher (blinded) who has been trained with a statistical analysis program will analyse the data using the Statistical Package for the Social Sciences version 27.0, IBM, New York, United States of America [55,56].

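### Table 1 describes improvement in self-efficacy as scoring above 70% of the SESPPFE, a level that makes no reference to the baseline score

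*Protocol article*

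**What the plan says.** In the protocol article, the SESPPFE row of Table 1 gives the outcome as "Improving self-efficacy by scores of higher than 70% of the self-efficacy scale for practicing pelvic floor exercise questionnaire (SESPPFE"). The same cell continues: "To measure the self-efficacy score at baseline, one-month, and two-months post-interventions". No other place in the article says what counts as improvement in self-efficacy.

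Section 2 (Materials and Methods) then uses the idea of improvement: "The time recorded by the pregnant women will be analysed with the self-efficacy improvements and adherence towards PFMT".

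Entry is not restricted by self-efficacy or by previous training skill. Apart from Malaysian citizenship, the inclusion criteria are "pregnant women aged over 18 years old, (2) any parity at 26–27 weeks’ gestation, (3) with either stress UI or mixed UI", and the exclusions are medical: "pregnant women with chronic medical problem(s) before pregnancy, complicated pregnancies, or conditions with which it is not advisable to practise PFMT will be excluded".

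Section 2.2 names a model for adherence only: "Exploratory analysis of the effect sizes for PFMT adherence will be conducted by mixed-effects regression analyses, controlling for significant baseline characteristics". The baseline characteristics it lists as examples are age, parity, education and income.

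**The concern.** Improving describes movement, whereas scoring above 70% describes position. A criterion that joins the two can misclassify in both directions. A woman who falls from 80% to 71% satisfies it, and a woman who climbs from 30% to 69% does not.

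Two kinds of statement are exposed. The first is any within-group claim that a given proportion of women improved, since some would meet the criterion before receiving anything. The second is the analysis of training time against self-efficacy improvements. The app logs training time, and Section 2 gives controls the app only after 36 weeks of pregnancy, so that analysis rests on the intervention arm without a randomised comparator. If women who are confident at entry also train more, which is plausible, a level-based definition could show an association between training time and improvement when nobody has changed. Two stated aims in the Introduction depend on these results: finding the appropriate training time, and assessing preliminary effectiveness on self-efficacy.

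**Working it through.** **1. What follows from the wording alone**

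Criterion as written: improved if the follow-up score exceeds 70% of the scale. Change is follow-up minus baseline.

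| Baseline | Follow-up | Change | Meets the criterion? |
|---|---|---|---|
| 80% | 71% | 71 − 80 = −9 points | yes |
| 80% | 80% | 0 | yes |
| 30% | 69% | 69 − 30 = +39 points | no |

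This step needs no outside figure. These scores are examples; the eligibility criteria rule out none of them.

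**2. The alternative reading**

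The phrase could be read as a rise of more than 70% of the scale. With a maximum of 100%, only a woman starting below 100 − 70 = 30% could then qualify. That is less natural and close to unattainable, and it too would need rewording.

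**3. Numbers per arm**

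The article states no figure for this outcome. Its sample size is used here only to turn proportions into counts. Section 2 says "A pilot randomised controlled trial for an expected small effect size should have 25 participants per arm" and allows 20% dropout: 25 / (1 − 0.20) = 31.25, rounded up to 32 per arm and 64 in total. The stated figure reproduces.

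**4. How many women could already be above 70% at entry**

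The article gives no SESPPFE mean or SD, so both are assumed. With a normal baseline, the share above the cut is 1 − Φ((70 − mean) / SD). With SD 15:

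| Assumed mean | z | Share above 70% | Of 32 |
|---|---|---|---|
| 55 | 1.00 | 0.159 | 5.1 |
| 60 | 0.67 | 0.252 | 8.1 |
| 65 | 0.33 | 0.369 | 11.8 |
| 70 | 0.00 | 0.500 | 16.0 |

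Widening the assumptions to mean 50 to 70 and SD 15 to 20 gives 9% to 50%, about 3 to 16 of 32.

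**5. What the criterion would count if nothing changed on average**

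Assume bivariate normal baseline (B) and follow-up (F) scores with equal means and SDs, correlation 0.6 to 0.8, and the wider ranges of step 4. Among women above 70% at follow-up:

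- Already above 70% at baseline: P(B > 70 and F > 70) / P(F > 70) = 0.38 (mean 50, SD 15, correlation 0.6) to 0.80 (mean 70, correlation 0.8).
- No rise in score: P(F > 70 and F ≤ B) / P(F > 70). With no true change, B and F are interchangeable, so this is half of the line above: 0.38 / 2 = 0.19 to 0.80 / 2 = 0.40.

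**6. Efficiency, only if the status above 70% is the variable analysed**

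The relative efficiency of a dichotomised normal score is φ(z)² / (p(1 − p)). At a median cut it is 0.637, and 0.637 × 32 = 20.4. If 25% exceed the cut it is 0.54, and 0.54 × 32 = 17.3. The article does not state that such an analysis will be done.

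**The case against.** The strongest reply is that a loosely worded table cell is being treated as a responder definition. The neighbouring EARS row has a similar form: it speaks of adherence rising from the lowest to the highest possible score, which can only be a direction and a scale range. The SESPPFE cell could likewise be a direction plus a benchmark, and its next sentence says a score will be measured at three times. Nowhere does the article say that women will be classified as improved or not. Section 2 also says the recorded time will be used to see which training skills change self-efficacy, which points towards comparison with baseline. Finally, the article condenses a fuller document, and modelling of a secondary questionnaire score is commonly left to that document.

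Much of this stands. It rules out several stronger conclusions that a reader might draw:

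- That the trial will test a dichotomised score, leaving 32 per arm worth about 20 or 17. Section 2.2 commits to no such analysis.
- That the 70% cut is built into the training-time analysis. Section 2 speaks of improvements there but mentions no threshold. The link exists only because Table 1 holds the sole criterion for improvement.
- That naming a mixed model for adherence alone shows the cut will be used for self-efficacy. That is silence, and the fuller document may settle it.
- That the comparison between arms is biased. Randomisation balances women already above 70% on average. They would dilute a contrast in the proportion above 70% but would not by themselves bias it.

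What the reply does not remove is the criterion itself. The point concerns something the article states, not something it omits: the cell attaches improvement to an absolute cut, and no other text in the article corrects it.

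**Conclusion.** The point holds as a defect in a stated criterion. Table 1 calls a level an improvement, although the baseline score is collected and women already above 70% may enrol. Read literally, it credits some women with no change or a fall, and misses large rises that end below the cut.

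The size is unknown, because the article gives no SESPPFE distribution. With a normal baseline, SD 15 and mean 55 to 70, between 16% and 50% of women would be above 70% at entry. A lower mean would make the share smaller, and women new to the exercises may well start low.

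The consequence is limited to within-group statements and to the training-time analysis, if Table 1 supplies its meaning of improvement. Table 1 lists self-efficacy as a secondary outcome in a pilot whose primary analysis is descriptive. Acceptability and usability, the primary outcomes, are unaffected, as is the sample size of 64. The correction is still worth making, because the results are meant to inform the later full trial.

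**What to change.** 1. Reword the SESPPFE row of Table 1 so that the outcome is the continuous score at one and two months, compared by arm with adjustment for the baseline score and the randomisation stratum (primigravida or multigravida).
2. In the training-time analysis of Section 2, use the baseline-adjusted score or change from baseline, and say which.
3. Report the proportion above 70% by arm at each visit, baseline included, as a level of self-efficacy and not as improvement.

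The cost is wording in Table 1, Section 2 and Section 2.2. The baseline score and the stratum are already recorded, so no new data, visits or participants are needed.

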## Data Availability

Not applicable.
